##### Sample size calculation:

To detect statistical significant difference of our main study parameter  $VO_2\text{peak}$  (ml/kg/min), between Fontan patients before and after treatment with enalapril, we calculated a group size of 52 will be sufficient. We calculated this sample size for paired observations with a clinical relevant effect of 10% elevation after treatment, with a mean of 33.5 and SD of 6.8 before treatment (Bossers et al.; J Thorac Cardiovasc Surg 2014) and an elevation of the mean to 36.85 with an expected same SD after treatment and calculated a SD of the difference of 6.8 with a correlation coefficient of 0.5. We used an alpha of 0.01 with 80% power. We used a lower alpha of 0.01 to correct for multiple comparison according to the Bonferroni correction, because we have five main study parameters. Moreover, we also need to take the change of drop out into account, which means we need 55 patients per group when we expect a 5% drop out. This means a group size of in total 55 Fontan patients and a group of 55 healthy subjects will be sufficient.

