## 6. Study parameters

### Main study parameters:

- *Cardiopulmonary exercise stress test*:  $VO_2$  peak.
- *Cardiac autonomic nervous activity*: heart rate variability and pre-ejection period.
- *Outcome of passive leg raising and head up tilt table testing*: cardiac output and cardiac autonomic tone.

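### Single-step Bonferroni at 0.01 for the five main parameters is valid but needlessly conservative; Holm's procedure keeps the same 5% overall error and rejects at least as much

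*Protocol*

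**What the plan says.** Under Sample size calculation (protocol section 4), the trial is sized on the before-after change in VO2peak: "We used an alpha of 0.01 with 80% power". The reason for that level follows: "We used a lower alpha of 0.01 to correct for multiple comparison according to the Bonferroni correction, because we have five main study parameters".

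Section 6, Main study parameters, gives the five: VO2peak; "heart rate variability and pre-ejection period" for autonomic activity; and "cardiac output and cardiac autonomic tone" as outcomes of leg raising and tilt testing.

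Section 7 (Data analysis, Statistics) names no significance level and no multiplicity procedure. The per-parameter level of 0.01 in the sample size section is therefore the only rule the protocol offers. Section 8 (Expected results) expects enalapril to improve exercise performance and the autonomic profile and to alter responsiveness to fluid loading and depletion. It gives directions, not sizes.

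**The concern.** Read as a decision rule, single-step Bonferroni declares a main parameter positive only if its own p-value is at most 0.01, whatever the other four show. Suppose one parameter has p = 0.012 and the other four are all well below 0.01. Bonferroni calls the fifth negative. Holm, at the same 5% familywise error and with no added assumption, calls it positive, because by then only one hypothesis remains and its threshold is 0.05.

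What is at stake is power for the second and later findings among the main parameters. The investigators expect effects in all three groups of main parameters, so this is not a remote case. How much is lost depends on how many of those effects are real and how large they are.

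**Working it through.** **Inputs from the protocol (Sample size calculation).** Baseline: "with a mean of 33.5 and SD of 6.8 before treatment". After treatment: "an elevation of the mean to 36.85 with an expected same SD after treatment". Paired variability: "calculated a SD of the difference of 6.8 with a correlation coefficient of 0.5". Alpha per test 0.01, power 80%, five main parameters, 5% dropout. Sidedness is not stated; two-sided is assumed.

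**Step 1: reproduce the plan's figures.**
- Difference: 36.85 − 33.5 = 3.35.
- SD of the difference: √(2 × 6.8² × (1 − 0.5)) = 6.8.
- Standardised effect: 3.35 / 6.8 = 0.493.
- Exact paired t-test, two-sided 0.01: power is 79.5% at n = 51 and 80.5% at n = 52. So n = 52, as stated.
- Other conventions do not give 52: two-sided normal approximation 49, one-sided t 45, one-sided normal 42. This supports the two-sided reading.
- Dropout: 52 / 0.95 = 54.7, so 55, as stated.
- Alpha: 0.05 / 5 = 0.01, as stated.

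**Step 2: thresholds.** Bonferroni compares all five p-values with 0.05/5 = 0.01. Holm orders them and compares the smallest with 0.05/5 = 0.01, the next with 0.05/4 = 0.0125, then 0.05/3 = 0.0167, 0.05/2 = 0.025 and 0.05/1 = 0.05, stopping at the first failure. The first threshold is the same and the later ones are larger, so Holm's rejections always include Bonferroni's.

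Exact single-test power for VO2peak at n = 52 at these five levels is 80.5%, 82.8%, 85.5%, 88.9% and 93.6%. These are the levels VO2peak could be tested at, depending on how many other parameters have been rejected before it.

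**Step 3: size of the gain.** Five paired t-tests were simulated at n = 52, 100,000 runs per scenario. VO2peak has its protocol effect of 0.493 SD. The effects of the other four, and the common correlation, are assumptions. VO2peak power, Bonferroni vs Holm:

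| Effect on the other four | Correlation 0 | Correlation 0.5 |
|---|---|---|
| None | 80.6% vs 80.7% | 80.5% vs 80.6% |
| 0.1 SD each | 80.6% vs 80.8% | 80.8% vs 80.8% |
| 0.25 SD each | 80.6% vs 82.6% | 80.9% vs 81.6% |
| 0.3 SD each | 80.5% vs 84.2% | 80.5% vs 82.1% |
| One at 0.493 SD, three none | 80.4% vs 82.4% | 80.6% vs 82.2% |
| Two at 0.493 SD, two none | 80.7% vs 84.8% | 80.4% vs 83.9% |
| 0.493 SD each | 80.4% vs 91.4% | 80.4% vs 89.0% |

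With all five at 0.493 SD and correlation 0.6, the figures are 80.5% vs 88.5%. The chance of rejecting all five, with all at 0.493 SD, is 34% vs 70% at correlation 0 and 51% vs 77% at correlation 0.5.

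**Step 4: checks.** The chance of at least one rejection was identical for the two methods in every scenario, as it must be with the same first threshold. No run had a hypothesis rejected by Bonferroni and kept by Holm. Holm's familywise error was at most 4.8%.

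**The case against.** The strongest reply is that nothing here is stated wrongly. Bonferroni is valid, the sizing is right, and 0.01 appears only in the sample size section, in the past tense. The actual testing rule may sit in a statistical analysis plan that is not at hand. Sizing at 0.01 is also the correct guaranteed-power calculation under Holm, so no design figure would change. All of this stands. What remains is that the protocol presents 0.01 as the correction for multiple comparisons and states no other rule. If only cautious sizing was meant, the sentence that settles the decision rule is the same one.

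A second reply concerns size, and it also stands. A reader might infer that the trial forgoes about 11 points of VO2peak power, or half its chance of showing all five effects (34% against 70%), on the plan's own inputs. The documents do not support that. The protocol gives an effect size for VO2peak only, and describes it as clinically relevant. It gives no effect, SD or correlation for the other four. Section 8 gives directions only, and one of its expectations, pulse wave velocity, concerns a secondary parameter. Section 1 cites a small study that found no effect of enalapril on exercise capacity. With moderate effects elsewhere the gain is a few points.

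A reader might also infer that the trial's ability to find any effect on its main parameters is impaired. It is not, since both methods start at 0.01.

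Finally, Bonferroni has simple matching simultaneous confidence intervals and Holm does not. That is a real but small advantage, and it does not make Bonferroni the better rule for reject-or-retain decisions.

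**Conclusion.** The point holds as a loss of efficiency, not as an error. For decisions on the five main parameters, Holm dominates single-step Bonferroni at the same 5% familywise error under any dependence.

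At n = 52 the gain in VO2peak power depends on what the other four parameters do:
- about 0 points if only VO2peak changes or the others change by about 0.1 SD;
- about 1 to 4 points if the others change by 0.25 to 0.3 SD;
- about 9 to 11 points if all five change by 0.49 SD and the correlation is 0 to 0.5 (8 points at 0.6).

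These figures assume two-sided tests, equal correlations, and effects for four parameters that the protocol does not supply. Reading 0.01 as the decision rule is a fair inference from the sample size section; the analysis section does not state it.

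**What to change.** Keep 52 evaluable and 55 enrolled Fontan patients, and keep the calculation at alpha 0.01. Describe it as guaranteeing 80% power for VO2peak whatever the other main parameters show.

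Add one sentence to section 7, and adjust the Bonferroni sentence in section 4 to match: the before-after tests of the declared main parameters will be judged by Holm's step-down procedure at an overall two-sided 5%. This must be fixed before the data are analysed. If an analysis plan exists, it should carry the same sentence.

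The cost is that sentence; no patients, visits or data are added. Because Holm has no equally simple matching simultaneous intervals, 99% confidence intervals can be shown beside the Holm decisions. A note should say that a parameter accepted at a later Holm step may have a 99% interval that includes no change.

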## **5. Treatment of subject:**

To all Fontan patients enalapril will be given twice daily at a dose of 0,5 mg/kg/day with a maximum of 20 mg per day. Enalapril will be titrated on average in two steps, by blood pressure measurements, which will be measured by the general practitioners of the patients. When a fall of more than 20% of the systolic blood pressure occurs, enalapril dosage will be lowered to a maximum acceptable dosage at which a fall of more than 20% of the systolic blood pressure does not occur. Dosage will also be lowered when Fontan patients feel light-headed or have complaints of dizziness. After a period of three months all procedures that are performed at the start of the study will be repeated.

This is a study of medicinal products within the meaning of the “WMO”. Which means preparation and labelling of the investigational medicinal products will be done according to the relevant GMP guidelines. The medicinal products in this study will be labelled and issued by the hospital pharmacy of the LUMC, which has a GMP license.

## 6. Study parameters

### Main study parameters:

- *Cardiopulmonary exercise stress test*:  $VO_2$  peak.
- *Cardiac autonomic nervous activity*: heart rate variability and pre-ejection period.
- *Outcome of passive leg raising and head up tilt table testing*: cardiac output and cardiac autonomic tone.

### Secondary study parameters:

- *Echocardiography*: Complete echocardiographic evaluation will be performed. This includes 2D imaging, colour Doppler and pulse wave velocity measurements of inflow and outflow through the cardiac valves. Tissue Doppler imaging as well as speckle tracking strain imaging will be performed. Special attention will be paid to hepatic venous blood flow patterns and superior caval venous (Glenn) flow patterns.
- *Cardiopulmonary Exercise Stress Testing*: A symptom limited maximal exercise stress test will be performed on a bicycle ergometer. During the stress test heart rate, and carbon dioxide production will be measured. This enables the assessment of maximal oxygen consumption,  $VE/VCO_2$  relationship and the measurement of the Oxygen Uptake Efficiency Slope (OUES).
- *Blood Sampling*: From a venous puncture blood will be taken to assess electrolytes (Na and K), kidney function (Creatinine and Urea), liver function (ASAT, ALAT, alkaline phosphatase, gamma globulin and bilirubin levels), albumin and NT-pro BNP levels.
- *24-hour monitoring of electrocardiography and impedance cardiography*: To monitor ECG and ICG non-invasively, continuously during 24 hours we will use the VU-AMS device (De Geus et al 1995; Riese et al 2003; Van Lien et al 2013; Willemsen et al 1996). By the use of seven electrodes on the thorax this ambulatory device continuously records the electrocardiogram, impedance cardiogram and movement (by means of a three axial accelerometer). VU-AMS makes it possible to monitor non-invasively in a continuous way during daily life activities heart rate, heart rate variability, stroke volume and pre ejection period. Respiratory sinus arrhythmia (derived from the electrocardiogram and respiration) is a measure of the cardiac parasympathetic activity; the pre ejection period (derived from combining electrocardiogram and impedance cardiogram signals) is an index of cardiac contractility and a reflection of cardiac sympathetic control. Respiratory sinus arrhythmia measured by the VU-AMS is based on the peak-valley method. The time between two successive R peaks in the electrocardiogram (the inter beat interval) is calculated by the VU-AMS software. The difference between the shortest interval during inspiration and the longest interval during exhalation is defined as the respiratory sinus arrhythmia and is used as a measure of cardiac vagal

tone, representing the parasympathetic nervous activity. Pre-ejection period is defined as the time between the onset of the depolarization of the ventricles (reflected by the Q-onset in the electrocardiogram) and the opening of the aortic valves (reflected by the B-point in the impedance cardiogram) In addition, the impedance cardiogram can be used to assess stroke volume (changes).-

- *Aortic stiffness*: By means of the arteriograph the pulse wave velocity of the aorta can be measured (Horvath et al 2010). This measurement is a surrogate of aortic stiffness. By means of the arteriograph, pulse wave velocity, augmentation index and central blood pressure can be measured non-invasively in a reliable and easy way.

- *Outcome of passive leg raising and head up tilt table testing*: After the baseline cardiovascular parameters have been performed the patient will undergo a passive leg raising test and a head up tilt table testing. There will be a period of at least 30 minutes between the two tests to allow the circulation to return to baseline levels.

- Passive leg raising: By means of passive leg raising an easy, safe and reversible fluid load can be given. After stabilization aortic pulse wave velocity will be measured by the arteriograph, while using echocardiography changes in and hepatic venous blood flow can be measured. Cerebral blood flow will be measured by Doppler recordings.
- Head up tilt table testing: Passive head-up-tilt testing induces an easily and fast reversible unloading of the central blood volume. After stabilization aortic distensibility will be measured by the arteriograph, while using echocardiography changes in hepatic venous blood flow can be measured. Cerebral blood flow will be measured by Doppler recordings. A Finapres device will be used to continuously non-invasively measure blood pressure.

## **7. Data analysis**

The study has a cross-sectional between-subject design paired with prospective within-subject design. Baseline cardiovascular measurements will be compared between the Fontan patients and their age and gender matched healthy controls. Comparisons between the groups will be made using the independent T-test in case of normal distribution and Mann-Whitney U test in case of non-normal distribution (SPSS for Windows, recent version).

After a period of 3 months treatment with enalapril all baseline cardiovascular measurements will be repeated and compared to pre-treatment values (echocardiography, cardiopulmonary exercise stress testing, blood testing, 24-hour monitoring of electrocardiography and impedance cardiography, and aortic distensibility). Also the fluid challenge by passive leg raising as well as the depletion of central and splanchnic blood volume by head up tilt testing will be repeated and compared to pre-treatment values.

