## **SUMMARY**

**Rationale:** There is no consensus on the use of ACE inhibition in Fontan patients without ventricular dysfunction. Multiple centres prescribe enalapril on a routine base for patients with a Fontan circulation and a preserved ventricular function, while other centres have considerable doubt about its effectiveness. Too little research has been done to the effectiveness of ACE inhibition in Fontan patients. There are as yet no studies available that investigate the effect of ACE inhibition on various cardiovascular parameters in patients with a Fontan circulation. By studying the effect of ACE inhibition on cardiovascular parameters as systolic and diastolic ventricular function, cardiac output, and the sensitivity of the cardiovascular system to fluid changes, the basic effects of ACE inhibition on the cardiovascular system of Fontan patients will become more clear. This will result in a more appropriate selection of patients that will profit of the use of ACE inhibitors.

**Main objective:** To treat Fontan patients for 3 months with the ACE inhibitor enalapril and compare a set of cardiovascular measurements before and after treatment in order to study its effect on the cardiovascular system and the effect of a reversible fluid challenge and depletion in Fontan patients, and to correlate all these results with the results of a symptom limited maximal exercise test.

**Study design:** This study consists of a longitudinal intervention study and a cross-sectional study.

**Study population:** 55 patients with a univentricular heart after palliation with the Fontan circulation will be included from an age of 8 until 18 years old. Patients who already use enalapril will be excluded. A number of fifty healthy age and gender matched subjects will serve as controls.

**Intervention (if applicable):** To all Fontan patients enalapril will be given twice daily at a dose of 0,5 mg/kg/day with a maximum of 20 mg per day. All Fontan patients will undergo all the investigations before and after treatment and healthy controls will undergo all the investigations once, except for blood testing and the symptom limited exercise test which will not be performed in healthy controls.

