#### **4. Study population**

##### Population:

Patients, who have been operated in the Leiden University Medical Centre (LUMC), with a univentricular heart after palliation with the Fontan circulation will be included. We strive for including 55 patients. A number of 55 healthy age and gender matched subjects will serve as controls.

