##### Inclusion criteria:

Patients with a univentricular heart after palliation with the Fontan circulation from 8-18 years old.

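### The baseline comparison with age- and sex-matched controls uses tests that ignore the matching, which costs precision if age and sex predict the outcomes

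*Protocol*

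**What the plan says.** Protocol section 7 describes the between-group part of the study as follows: "Baseline cardiovascular measurements will be compared between the Fontan patients and their age and gender matched healthy controls". The next sentence fixes the test: "Comparisons between the groups will be made using the independent T-test in case of normal distribution", with the Mann-Whitney U test as the alternative when the data are not normal. The Summary and sections 3 and 4 also call the controls matched on age and gender. No section names a paired test, a model for matched sets, or adjustment for age and sex.

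The inclusion criterion covers a wide span of growth: "Patients with a univentricular heart after palliation with the Fontan circulation from 8-18 years old".

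Section 4 plans equal groups: "We strive for including 55 patients" and "A number of 55 healthy age and gender matched subjects will serve as controls". The Summary differs: "A number of fifty healthy age and gender matched subjects will serve as controls". The protocol does not say whether matching is individual (one control chosen for each patient) or by group (similar age and sex distributions).

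The first two objectives in section 2 are comparisons with healthy subjects: autonomic and vascular function, and the response to tilt and leg raising. The sample size paragraph addresses only the before-after change in VO2peak in patients, with "We used an alpha of 0.01 with 80% power". No power or alpha is stated for the patient-control comparison.

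**The concern.** Matching on age and sex makes the two groups alike on those variables. If the variables also drive the outcome, the difference in means varies less from sample to sample than it would between two unrelated groups. An independent t-test or Mann-Whitney test does not know this. It leaves the variation due to age and sex in the error term and reports a standard error larger than the true one.

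Between 8 and 18 years it is plausible that age and sex explain some of the variation in heart rate variability, pre-ejection period and pulse wave velocity. Choosing them as matching variables presupposes as much. What is at stake is the precision of the comparisons behind the first two objectives: intervals wider than necessary, and real differences that may be missed. This is not a detail left open for a later analysis plan. The protocol names the tests, and a plan that followed it would inherit them.

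**Working it through.** **1. The protocol's own figure.** Inputs from the sample size paragraph: mean 33.5 rising to 36.85 (difference 3.35), SD 6.8 at both times, before-after correlation 0.5, alpha 0.01, power 80%.

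SD of the difference = sqrt(6.8² + 6.8² − 2 × 0.5 × 6.8 × 6.8) = 6.8.

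A two-sided paired t-test (noncentral t) needs n = 52, which agrees with the protocol. Allowing 5% dropout, 52 / 0.95 = 54.7, rounded up to 55. This figure is right and is not touched by the point made here. The 0.5 in it is the correlation between two measurements in one patient, not between a patient and a control.

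**2. Effect of ignoring the matching.** Let ρ be the correlation that matching induces between a patient and the matched control, with common SD σ and n per group.

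- True variance of the difference in means: 2σ²(1 − ρ)/n
- Variance used by the independent t-test: about 2σ²/n
- Ratio of reported to true standard error: 1/√(1 − ρ)

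**3. Numbers.** From the protocol: n = 55 per group. Assumed, because the protocol gives none of them: ρ from 0 to 0.5, a true difference of 0.5 SD, and alpha. Two-sided 0.05 is shown first, then 0.01 in case the protocol's Bonferroni level is carried over. Paired power uses the noncentral t. Unmatched power uses a normal approximation with the t critical value.

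| ρ | SE ratio | Power at 0.05, unmatched | Power at 0.05, paired | Power at 0.01, unmatched | Power at 0.01, paired |
|---|---|---|---|---|---|
| 0 | 1.00 | 73.9% | 73.1% | 50.0% | 48.6% |
| 0.1 | 1.05 | 75.0% | 77.5% | 50.0% | 54.1% |
| 0.2 | 1.12 | 76.3% | 82.1% | 50.0% | 60.5% |
| 0.3 | 1.20 | 77.8% | 86.8% | 50.0% | 67.8% |
| 0.5 | 1.41 | 81.7% | 95.4% | 50.0% | 84.6% |

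The true false-positive rate of the unmatched test at nominal 5% is about 3.7%, 2.7%, 1.8% and 0.5% at ρ = 0.1, 0.2, 0.3 and 0.5. It stays below nominal whenever ρ is positive.

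**4. Group matching and unequal numbers.** Individual pairs are not established, so the same question was simulated with 55 patients and 50 controls balanced on age and sex but not paired (0.5 SD difference, alpha 0.01). If age and sex explain 20%, 30% or 50% of the outcome variance:

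- t-test: false-positive rate about 0.4%, 0.2% and 0.03%; power about 46%, 47% and 47%.
- Linear model with group, age and sex: false-positive rate about 1%; power about 58%, 67% and 84%.

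The mechanism therefore does not depend on 1:1 pairing.

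**The case against.** **The size is assumed.** This stands. The protocol gives no patient-control correlation. For age and sex alone to produce ρ = 0.5, they would have to explain about half the outcome variance, including among heterogeneous Fontan patients, and nothing in the protocol shows that. At ρ = 0.1 the gain is 2.5 percentage points, and at zero there is none. The loss also shrinks for large differences: at 0.8 SD both analyses exceed 98% power at alpha 0.05 and 93% at 0.01.

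**The unmatched test is safe.** This also stands. A reader might infer that the p-values and intervals are simply invalid. They are not: the estimated mean difference is unchanged and the error is in the conservative direction.

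**A paired test may not be feasible.** Fair. The protocol does not describe 1:1 matching, and the Summary's 50 controls would leave some of the 55 patients without a partner. This argues for a covariate-adjusted model, not for leaving age and sex out.

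**Body size.** Because cardiac output is listed without units, a reader might infer that it will be analysed in absolute terms and that a group difference could merely reflect body size. The protocol does not support that. It never says how cardiac output will be expressed, and its parameter lists give no unit for VO2peak either. Cardiac output is also listed as an outcome of leg raising and tilt, and may be expressed relative to the resting value. Indexing is a detail that an analysis plan commonly settles.

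**Conclusion.** The point holds as one of efficiency. Section 7 states a matched comparison and assigns it tests that discard the matching. If age and sex predict the outcomes, standard errors are overstated by 1/√(1 − ρ). With 55 per group, a 0.5 SD difference and alpha 0.05, power changes by about −1, +2.5, +6, +9 and +14 points at ρ = 0, 0.1, 0.2, 0.3 and 0.5 when the matching is used. At alpha 0.01 and ρ = 0.3 the gain is about 18 points (50% to 68%).

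The direction rests on ρ being positive, which is the premise of matching. The size rests on assumed values of ρ, effect and alpha, so no single figure should be taken as the loss in this trial. Controls have no exercise test, so the powered VO2peak comparison is outside the point altogether. The change is worth making because it costs little and bears on two stated objectives.

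**What to change.** In section 7, replace the unmatched tests for the baseline patient-control comparison with a linear model for each outcome containing group, age and sex, with the outcome transformed if skewed. Report the adjusted group difference with its confidence interval. The model is valid under individual or group matching and with unequal numbers.

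Use a paired analysis (paired t-test or Wilcoxon signed-rank) only if matching is confirmed as strictly 1:1. State how controls are matched, and reconcile the 50 controls in the Summary with the 55 in section 4.

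The cost is a change of wording. No extra participants are needed, and age and sex are already required for matching. The statistical price is a few degrees of freedom and an assumption that the outcome is roughly linear in age, which can be checked from residuals.
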